#### Screening and consent

A trained research assistant will conduct a brief phone pre-screening with all interested prospective participants. During this call, the research assistant will collect key demographic information (e.g., age, sex, education level, and smartphone ownership) and administer two validated screening tools: the Quick Mild Cognitive Impairment screen (QMCI, a clinician-administered tool used to assess objective cognitive status [27]) and the Physical Activity Readiness Questionnaire (PAR-Q, which evaluates the participant’s ability to safely engage in moderate exercise [26]; (see Table 2)). Both assessments will require fewer than five minutes to complete. Participants must achieve a QMCI score at or above the specified age- and education-adjusted scoring thresholds that indicate either CN or MCI status (see Table 1 [29, 30]) and report no contraindications to performing moderate-intensity exercise on the PAR-Q. Subjects who score below these thresholds will be excluded from the trial; no borderline adjudication process will be applied to ensure clarity and reproducibility.

**Table 2 Tab2:** Screening questionnaires

Questionnaire	Description and variables collected
Basic Info Screening Form (eligibility criteria)	Age, whether prospective subjects own and can operate a smartphone/computer device
Physical Activity Readiness Questionnaire (PAR-Q)	Safe for participants to perform moderate-level exercise. This will be the main factor in determining if it is safe to perform the moderate-intensity exercise routine for participants; an emergency plan is detailed later in the study
Quick Mild Cognitive Impairment screen (QMCI) 6-item	A clinician-administered tool used to assess objective cognitive status

Table describes the screening questionnaires that will be to evaluate the eligibility of each prospective participant as well as a descriptive identification of which variables of particular interest will be collected

Individuals meeting these pre-screening criteria will then be scheduled for an in-person screening visit to provide written informed consent and further assess eligibility criteria via a 7-day screening period. After signatures are obtained, each prospective subject will be provided with a copy of the signed informed consent document. All procedures have been approved by the University of Miami Institutional Review Board (IRB) requirements and federal privacy protections and will be conducted in accordance with the Helsinki Declaration. Thereafter, prospective participants will be randomized into one of three arms and will receive intervention-specific, wearable devices and will be instructed on how to use these devices. All prospective participants will receive Fitbit devices, while those assigned to sleep or sleep + exercise intervention will receive an Elemind Neuromodulation headband to be used daily without stimulation during the initial 7-day screening period and a Lys device. Prospective participants in all groups will be asked to wear the Fitbit device continuously to establish baseline physical activity levels and to confirm sedentary to lightly active physical activity levels in order to satisfy eligibility criteria for those assigned to interventions that involve exercise, and those assigned to the sleep-only or sleep + exercise interventions will be asked to wear the Elemind Neuromodulation headband without stimulation while the device actively collects sleep data for seven consecutive nights to establish baseline sleep patterns, ensure comprehension of and comfortability with wearing the headband; additionally, this will confirm subquality sleep pre-intervention to satisfy eligibility criteria for those assigned to groups that involve the sleep intervention.

Prospective participants who are assigned to the sleep or sleep + exercise interventions and are determined to have good quality sleep after the onboarding period as defined by the eligibility criteria will either be reassigned to the exercise-only intervention (if also found to engage in < 150 minutes of moderate-level or < 75 minutes of vigorous-level activity weekly via the Fitbit) or will be excluded from further participation and given $20 compensation. Prospective participants who are assigned to the exercise or sleep + exercise interventions and who are found to be active or very active (as defined by the eligibility criteria) will either be reassigned to the sleep-only intervention and be invited to undergo an additional 7-day onboarding screening duration with the Elemind Neuromodulation headband to determine sleep-specific eligibility or will be excluded from further participation and given $20 compensation. Prospective subjects who agree to undergo an additional 7-day screening period and are deemed to have good quality sleep pre-intervention at baseline will also be excluded from participation and given $20 compensation.

Once a participant has completed the 7-day onboarding screening period and found to be eligible, subjects will be prompted to set up an appointment with Quest Diagnostics. Sample analysis will be available to the participant through email and/or through the Quest Diagnostics app within a few days, and participants will consent to share the data with the University of Miami study team. Intervention (week 0) will begin as soon as possible after this process is complete. Another identical procedure will be initiated as soon as possible after the intervention period is complete. All procedures will comply with the University of Miami Institutional Review Board (IRB) requirements and federal privacy protections. Subsequent to completing the onboarding screening period, eligible participants will be invited to complete an in-person baseline visit.

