Prospective participants will be excluded in the case of (1) severe mobility limitation(s) that prevent(s) safe participation in moderate exercise protocols; (2) unstable or uncontrolled medical conditions (e.g., recent cardiovascular event (≤ 6 months), cerebrovascular accident or transient ischemic attack (≤ 6 months), active cancer, or uncontrolled diabetes) that pose safety concerns; (3) inability to complete intake screening procedures; (4) severe uncorrected hearing impairment, particularly if it precludes effective utilization of the Elemind Neuromodulation headband, and/or vision impairment that interferes with digital device usage or in-person exercise guidance; (5) determined to have Alzheimer’s/dementia based on performance on the Quick Mild Cognitive Impairment (QMCI [27]; see Table 1); (6) inability or unwillingness to learn or engage with digital devices (e.g., smartphone, Fitbit, Elemind, or Lys), even with staff support; (7) regular pre-study engagement in ≥ 150 minutes of moderate-level and/or ≥ 75 minutes of vigorous-level exercise per week based on Fitbit data obtained during the initial 7-day onboarding screening period; (8) determined to have adequate sleep metrics, including duration (mean 7–9 hours) and quality (sleep efficiency ≥ 80% [28]), pre-intervention based on Elemind Neuromodulation headband data obtained during the initial 7-day onboarding screening period; and (9) current usage of disease-modifying therapy targeting amyloid (e.g., anti-amyloid monoclonal antibodies) or tau.

**Table 1 Tab1:** Quick Mild Cognitive Impairment score thresholds by cognitive status

	**Aged ≤ 75, education < 12 years**	**Aged ≤ 75, education ≥ 12 years**	**Aged > 75, education < 12 years**	**Aged > 75, education ≥ 12 years**
CN	≥ 66	≥ 70	≥ 64	≥ 64
MCI	55–65	58–69	51–63	52–63
Dementia	< 55	< 58	< 50	< 51

Table describes the score thresholds of the Quick Mild Cognitive Impairment screening tool to suggest cognitive status (i.e., cognitively normal, mild cognitive impairment, or dementia) based on adjustments for dichotomized age and educational attainment. Higher scores indicate better cognitive function. *CN*, cognitively normal; *MCI*, mild cognitive impairment; *QMCI*, Quick Mild Cognitive Impairment screen

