#### Participant recruitment

A total of 60 participants comprised of approximately 30 CN older adults and 30 older adults with MCI will be enrolled in this study. Recruitment strategies will consist of a combination of the following:Participants will be recruited from existing studies and research registries maintained by the Translational Sleep and Circadian Sciences (TSCS) Laboratory at the University of Miami Miller School of Medicine. All individuals considered for enrollment will have previously consented to be contacted for future research opportunities. Initial contact will be made via phone by trained study personnel to confirm interest and screen for eligibility.In addition, recruitment will include referrals for prospective participants with an MCI diagnosis from the Division of Cognitive Neurology at the University of Miami.Moreover, flyers and social media advertisements will be distributed throughout southern Florida to further aid in recruitment efforts.This trial will participate in the University of Miami’s Consent to Contact program, which allows approved researchers to access a database of University of Miami Health System patients who have agreed to be contacted about participating in clinical research studies.

Recruitment and enrollment procedures will comply with all institutional and federal guidelines, including the Health Insurance Portability and Accountability Act (HIPAA), to ensure privacy and confidentiality of all protected health information that is obtained. Eligible participants will be equally randomized (*n* = 20 per group) into three study arms: sleep-only, exercise-only, or combined sleep and exercise. Stratified randomization by cognitive status will be employed to ensure balanced representation across groups (i.e., each group will be comprised of 10 CN participants and 10 participants with MCI).

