#### Randomization

The design will follow CONSORT randomization guidelines [31]. Participants will be eligible for randomization once all baseline questionnaires are completed. Blocked randomization will be conducted using a randomization table. Subjects in each block will be assigned to one of three intervention arms, ensuring equal allocation between CN and MCI subjects in each group.

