#### Baseline and follow-up visits

Data will be collected at baseline, biweekly, and at the 8-week follow-up to assess changes in sleep, exercise, biomarkers, and cognition. After consent and randomization, participants will be onboarded in person to each intervention-specific device and observed for a 7-day period prior to the baseline visit to establish baseline sleep patterns and/or physical activity levels relevant for each assigned intervention and to ensure all eligibility criteria are satisfied. Cognitive function will be measured using an augmented reality-based tool at baseline and week 8, with brief pulse assessments administered twice-weekly throughout the intervening period. Blood biomarkers will be collected via venipuncture at Quest Diagnostics (baseline and week 8). Physical activity and sleep data will be respectively monitored using Fitbit (all groups) and the Elemind headband (sleep and sleep + exercise groups), and light exposure will be tracked via the Lys device (sleep and sleep + exercise groups). Participants will also complete validated self-report surveys (e.g., PASE, CHAMPS–MET, PROMIS instruments) to capture psychosocial and behavioral variables at weeks 0 and 8. This multimodal approach will enable temporally-aligned, comprehensive data capture across digital and self-reported domains (see Table 3).

**Table 3 Tab3:** Timeline of questionnaires provided

Variable	Screening	Baseline	8-week
Basic Info Screening Form (eligibility criteria)	X		
Physical Activity Readiness Questionnaire (PAR-Q)	X		
Quick Mild Cognitive Impairment screen (QMCI), 6-item	X		
Demographic Questionnaire		X	
Chronic Health Questionnaire		X	X
PROMIS Self-reported Cognitive Functioning Behaviors Short Form		X	X
PROMIS Sleep Disturbance 4a		X	X
PROMIS Emotional Support 4a short form		X	X
PROMIS Depression 4a shot form		X	X
PROMIS Anxiety 4a short form		X	X
PROMIS Social Isolation 4a		X	X
General PROMIS Life Satisfaction 5a		X	
Cross Ethnic-Racial Identity Scale		X	
PASE Physical Activity Questionnaire (exercise and sleep + exercise interventions only)		X	X
CHAMPS-MET Physical Activity Questionnaire (exercise and sleep + exercise interventions only)		X	X

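### Randomisation comes before arm-specific eligibility checks that exclude or reassign people, so the three arms differ by post-randomisation selection, and other sections of the article contradict this order

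*Protocol article*

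**What the plan says.** All references are to the protocol article.

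**The operational description**
- Screening and consent, after written consent: "Thereafter, prospective participants will be randomized into one of three arms and will receive intervention-specific, wearable devices". Baseline and follow-up visits gives the same order: "After consent and randomization, participants will be onboarded in person to each intervention-specific device and observed for a 7-day period".
- The 7-day check depends on the arm. All arms wear the Fitbit, but its purpose is "to confirm sedentary to lightly active physical activity levels in order to satisfy eligibility criteria for those assigned to interventions that involve exercise". The headband goes only to the two sleep arms, and the sleep criterion is confirmed only there.
- Good sleepers in sleep-only or combined "will either be reassigned to the exercise-only intervention" if also below the activity limits, or are excluded. Active people in exercise-only or combined "will either be reassigned to the sleep-only intervention and be invited to undergo an additional 7-day onboarding screening duration", or are excluded. No route leads into combined. Compensation and parking reimbursement adds that the person's interest in another arm also decides whether a move happens.

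**The conflicting description**
- Participants lists high activity (exclusion 7) and being "determined to have adequate sleep metrics" (exclusion 8) as exclusions for everyone.
- Participant recruitment says that eligible people are randomised, 20 per arm, and that "each group will be comprised of 10 CN participants and 10 participants with MCI".
- Randomization: "Participants will be eligible for randomization once all baseline questionnaires are completed". Table 3 places those questionnaires at the baseline visit, which follows the 7-day screen.

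The Analysis plan makes the group × time term the main test of efficacy, and its primary goal is to find which arm improves most. The article does not say in which arm a reassigned person is analysed.

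**The concern.** Randomisation makes arms comparable only if what happens afterwards does not select people differently by arm. Here the selection rule is itself arm-specific, and it acts on baseline sleep and activity. The Objectives section hypothesises that both are linked to cognition and biomarkers. If people with good baseline sleep or high baseline activity change differently over 8 weeks, that difference enters the group × time term and cannot be told apart from an intervention effect. The combined arm, hypothesised to do best, is the only one selected on both deficits. The article gives sleep-only participants a Fitbit so that activity does not confound the sleep effect, yet the same procedure can move active people into that arm. Because the results are meant to guide power calculations for a full trial, distorted effect sizes would carry forward.

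**Working it through.** **Step 1. Who can be in each arm.**

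| Arm | Sleep tested | Activity tested | Can receive reassigned people | Final population |
|---|---|---|---|---|
| Exercise-only | no (no headband) | yes | good sleepers who are inactive | inactive, any sleep |
| Sleep-only | yes | no | active people who sleep poorly | poor sleepers, any activity |
| Combined | yes | yes | none | inactive poor sleepers |

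This follows from the text alone, with no figures assumed.

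**Step 2. Size.** The article gives no share of good sleepers (g) or active people (a), and no acceptance rate for a move (c). I assume the first allocation is 1:1:1, that sleep and activity status are independent, and that accrual stops at 60 retained without refilling arms. Per one person allocated to each arm, those retained are:
- exercise-only: (1−a) + 2c·g(1−a)
- sleep-only: (1−g) + 2c·a(1−g)
- combined: (1−g)(1−a)

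Check: at g = a = 0 this gives 1/1/1, the planned 20/20/20.

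Illustration, g = 0.30, a = 0.25, c = 1:
- exercise-only: 0.75 + 2×0.30×0.75 = 1.20
- sleep-only: 0.70 + 2×0.25×0.70 = 1.05
- combined: 0.70×0.75 = 0.525
- total 2.775, or about 26/23/11 of 60
- good sleepers in exercise-only: (0.225 + 0.45)/1.20 = 56%; elsewhere 0%
- active people in sleep-only: (0.175 + 0.35)/1.05 = 50%; elsewhere 0%
- placed by reassignment: (0.45 + 0.35)/2.775 = 29%

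Over g 0.20–0.40, a 0.15–0.35 and c 0.5–1, the reassigned share runs from 11% to 36%, and combined receives 9 to 16 of 60.

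**Step 3. Exclusion only (c = 0).** Good sleepers are still 0.225/0.75 = 30% of exercise-only, and active people 0.175/0.70 = 25% of sleep-only, against 0% elsewhere. Dropping reassignment alone therefore does not cure the problem.

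**Step 4. Effect on the test.** A null simulation (20,000 runs, 20 per arm, no intervention effect, only exercise-only containing good sleepers) assumed that good sleepers' change differs by d SD. The bias is share × d.

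| Good sleepers in exercise-only | d | Bias (SD) | Three-arm test rejects (nominal 5%) |
|---|---|---|---|
| 30% | 0.3 | 0.09 | 5.6% |
| 30% | 0.5 | 0.15 | 7.2% |
| 30% | 0.8 | 0.24 | 11.0% |
| 56% | 0.3 | 0.17 | 7.4% |
| 56% | 0.5 | 0.28 | 12.7% |
| 56% | 0.8 | 0.45 | 26.0% |

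With a 0% share in every arm the rejection rate is 5.0%.

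**The case against.** **Planned adjustment.** Adherence and engagement names baseline sleep, baseline activity and cognitive status as covariates, and PROMIS Sleep Disturbance is collected in all arms. This helps only in part. The mixed model in the Analysis plan does not list these covariates. As main effects they would, with complete data, leave the group × time estimate unchanged. Headband baseline sleep does not exist in exercise-only, PROMIS is not the eligibility measure, and combined contains no good sleepers or active people to adjust over. Sleep-only versus combined could be partly rescued by restricting to inactive people in the arm first allocated, since both arms have headband and Fitbit data. The exercise-only comparisons cannot be rescued this way.

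**Materiality.** Group × time compares changes, so bias needs change itself to depend on baseline status. The article hypothesises associations and does not establish causes. At a 30% share and 0.3 SD the inflation is trivial (5.6%). This is fair: the selection is certain under the written procedure, but its effect is not quantified by the documents. The exploratory label does not remove the problem, because the stated primary goal is to compare arms.

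**Stronger readings a reader might infer.**
- *Staff place people by hand, or the move is automatic.* The text gives no mechanism, and allows exclusion or refusal instead of a move.
- *The trial is no longer randomised.* On the grid above, 64–89% of those retained stay in their allocated arm.
- *The arms will end 26/23/11.* Refilling to 20 per arm is neither stated nor ruled out. It would restore counts, not comparability.
- *The reassignment rule admits very active people.* It joins the two activity limits with 'or', where the complement of exclusion 7 needs 'and'. Read alone, 300 moderate and 0 vigorous minutes would pass, but exclusion 7 still bars that person. This is a drafting slip.

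**Conclusion.** The point holds as a design flaw together with an internal contradiction. Three sections settle eligibility for everyone or place randomisation after baseline questionnaires. Screening and consent and Baseline and follow-up visits randomise first, and Screening and consent then selects by arm. Followed as written, that makes the arms different populations, and nothing else in the article cures it. The 20/20/20 and 10 CN/10 MCI balance is unprotected once people move or leave, though whether it would actually be lost is not determined. Every percentage above is illustrative and rests on assumed prevalences, independence and acceptance. The direction of selection (good sleepers only in exercise-only, active people only in sleep-only) does not depend on those figures. It should be corrected before participants are randomised under this procedure.

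**What to change.** Reconcile the sections so that there is one sequence:
1. Everyone wears both the Fitbit and the headband, without stimulation, for the 7-day screen.
2. Exclusions 7 and 8 are applied to all, as Participants already states, with thresholds unchanged.
3. Baseline is completed.
4. Participants are then randomised, stratified by cognitive status.

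Delete the reassignment rule, which also makes its 'or' wording moot. If people eligible for only one arm are to be kept, follow them as a non-randomised descriptive cohort outside the group × time analysis.

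**Cost.** A protocol amendment and materially more screening. On the illustrative inputs:
- Current procedure: 60/(2.775/3) ≈ 65 consented. Headbands are lent to two-thirds of them (about 43) plus active exercise-only people offered a second screen (65/3 × 0.25 ≈ 5), about 49 in all.
- After the fix: 60/(0.70×0.75) ≈ 114 consented, all lent a reusable headband for a week.
- Screen failures rise from about 5 to about 54. At the article's $20 each, that is about $1,080 rather than $100, besides staff time for onboarding.

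Across wider assumptions, the number consented runs from 75 (10% good sleepers, 10% active) to 172 (50% and 30%). Participants, read literally, already implies these screen failures.

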### Interventional group 1 (exercise only)

Participants randomized to the exercise-only group will engage in an 8-week, home- and site-based exercise intervention designed for older adults across a range of cognitive and physical function levels. All site-based sessions will occur in-person at the study facility under supervision of trained staff. Each week, participants will attend two 60-minute structured exercise sessions, consisting of aerobic training and resistance training. On the remaining five days when subjects will not engage in structured exercise, subjects will be asked to engage in 30 minutes of moderate-intensity walking activities. In-lab exercise protocols will be fully standardized to ensure consistency of exercise dosage and fidelity across participants. The target exercise load will be 270 minutes of moderate-intensity exercise weekly for 8 weeks. Although considered short-term exercise, this exercise dosage has been shown to improve cerebral blood flow, regional brain volume, and brain-protective trophic factors [32].

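### The activity condition for moving good sleepers into the exercise-only arm is not the complement of exclusion criterion 7, so anyone reaching exactly one limit is barred by one rule and admitted by the other

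*Protocol article*

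**What the plan says.** The activity limit appears in three places in the protocol article.

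- **Participants, exclusion criterion 7.** The bar is "regular pre-study engagement in ≥ 150 minutes of moderate-level and/or ≥ 75 minutes of vigorous-level exercise per week based on Fitbit data", measured in the 7-day onboarding period. Reaching either limit, or both, excludes.
- **Screening and consent, purpose of the Fitbit week.** The device is worn "to confirm sedentary to lightly active physical activity levels in order to satisfy eligibility criteria for those assigned to interventions that involve exercise".
- **Screening and consent, reassignment.** Two consecutive sentences apply. The first concerns people assigned to sleep-only or sleep + exercise who turn out to sleep well. They may move to exercise-only "if also found to engage in < 150 minutes of moderate-level or < 75 minutes of vigorous-level activity weekly"; otherwise they are excluded. The second concerns people assigned to exercise-only or sleep + exercise "who are found to be active or very active (as defined by the eligibility criteria". They may move to sleep-only after a further week of sleep screening; otherwise they are excluded.

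Exclusion criterion 7 is the only activity threshold in the eligibility list, so the second sentence must refer to it.

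**The concern.** The reassignment condition looks like an attempt to restate criterion 7 from the eligible side. When a rule that bars on either of two limits is turned round, the 'or' must become 'and'. Here it stayed 'or', which leaves a test that almost any one-sided exerciser passes: a person with no vigorous minutes meets it however much moderate exercise they do.

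The exercise-only arm is meant to take people who are not already exercising at the excluded level. If the literal condition is applied, some people the protocol defines as too active can enter by this route, which would weaken the change in activity that the arm is meant to produce. Two staff members working from different sections could also decide the same person's eligibility differently.

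**Working it through.** No sample size, power or alpha figure depends on this point, so there is no figure of the plan's to reproduce. The check is logical.

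**Inputs.** M is weekly moderate minutes and V is weekly vigorous minutes, both from the Fitbit week. The limits of 150 and 75 are those in criterion 7 and in the reassignment sentence.

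**The two rules.**

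- Criterion 7: barred if M ≥ 150 or V ≥ 75. Its complement (eligible) is M < 150 **and** V < 75.
- Reassignment to exercise-only: admitted if M < 150 **or** V < 75. It fails only if M ≥ 150 and V ≥ 75.

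**Test cases.**

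| M | V | Criterion 7 | Reassignment condition | Agree? |
|---|---|---|---|---|
| 149 | 74 | eligible | admitted | yes |
| 150 | 0 | barred | admitted (0 < 75) | no |
| 300 | 0 | barred | admitted (0 < 75) | no |
| 0 | 75 | barred | admitted (0 < 150) | no |
| 0 | 120 | barred | admitted (0 < 150) | no |
| 150 | 75 | barred | not admitted | yes |

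The rules agree when both values are below their limits or both are at or above them. They conflict whenever exactly one limit is reached.

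**Enumeration.** Take every whole-minute pair with M from 0 to 300 (301 values) and V from 0 to 150 (151 values), 301 × 151 = 45,451 pairs.

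- Both below: 150 × 75 = 11,250.
- Both at or above: 151 × 76 = 11,476.
- Exactly one reached: 151 × 75 + 150 × 76 = 22,725.

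Criterion 7 bars 22,725 + 11,476 = 34,201 pairs, and the reassignment condition admits 22,725 of them. With 'and' in place of 'or', the rules disagree on 0 pairs. These are counts of grid cells, which show the shape of the conflict; they say nothing about how many participants fall there.

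**Conflict within the reassignment paragraph.** Take a person assigned to sleep + exercise with good sleep, M = 300 and V = 0. Both sentences cover that assignment. The first permits a move into exercise-only, because 0 < 75. The second treats the person as too active under the eligibility criteria and offers only sleep-only screening or exclusion. Exclusion is available under both sentences, but the two reassignment destinations are incompatible. With 'and', the first sentence no longer admits this person, and both sentences keep them out of exercise-only.

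**Size per person.** The section on recruitment plans 20 people per arm, 10 per cognitive stratum. One person wrongly admitted is 1/20 = 5% of the exercise-only arm and 1/10 = 10% of a stratum within it.

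**The case against.** The strongest reply is that criterion 7 is a general exclusion, that the 7-day period is there to confirm all eligibility criteria, and that only people found eligible continue. On that reading the parenthesis adds a condition without waiving criterion 7, 300/0 and 0/120 stay excluded, and the 'or' is a slip in paraphrase. The next sentence, which refers back to the eligibility criteria, supports a slip.

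Part of this stands. The intention was very probably the complement of criterion 7. But criterion 7 is not a dependable backstop, because the section on screening and consent does not use it as a general bar. It ties the activity check to arms that involve exercise and lets people who fail it move to sleep-only. For a good sleeper coming from a sleep arm, the parenthesis is therefore the operative activity test. Nor can the conflict be removed by reading criterion 7 as requiring both limits, since its 'and/or' rules that out.

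It also stands that the scope is narrow. The 'or' wording governs one route only; people first assigned to exercise-only are judged by the eligibility criteria. The models include baseline physical activity as a covariate (Adherence and engagement), which may absorb some of the imbalance but does not settle who is eligible.

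A reader might infer more than the documents support:

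- **That moderate and vigorous minutes should be summed,** for instance as M + 2V < 150, because someone at 149/74 passes both rules. The article promises no combined rule and states no 2:1 equivalence, and it gives no other definition of the activity level it wants confirmed. A stricter threshold is a debatable preference.
- **That such a person gains no added dose,** since 149 + 2 × 74 = 297 exceeds the stated target ("The target exercise load will be 270 minutes of moderate-intensity exercise weekly for 8 weeks"). This needs the unstated 2:1 weight; in plain minutes the total is 149 + 74 = 223, below 270. It also needs the programme to replace existing activity, which the article does not say.
- **That different sites would decide differently.** The trial is single-center, so only disagreement between staff is possible.

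**Conclusion.** The point holds as a contradiction between two statements of one eligibility rule. Read literally, the condition for moving good sleepers into exercise-only admits everyone who reaches exactly one activity limit, all of whom criterion 7 bars, and it can send the same sleep + exercise assignee in two directions.

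Its reach is one reassignment route. The number affected is unknown, because the article gives no expected frequency of good sleepers in the sleep arms or of people who reach exactly one limit. Each person wrongly admitted is 5% of a 20-person arm. The conclusion rests on the literal wording of both sections and on the reassignment condition being applied as written; if staff apply criterion 7 throughout, no one is wrongly admitted and only the text is at fault. It should be corrected, but it does not call the overall design into question. Whether 150 and 75 minutes are the right limits is not judged here.

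**What to change.** Reconcile the two sections by making the reassignment condition the exact complement of exclusion criterion 7. Either replace 'or' with 'and', so that a person must be below both limits, or drop the numbers and write that the person must not meet exclusion criterion 7. The cross-reference is safer, because the limit is then stated once and the two sections cannot drift apart.

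This is a change of one word or one clause. It uses the same Fitbit week, adds no procedure and costs nothing. It turns away nobody whom criterion 7 does not already bar.
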